## Abstract

**Introduction:** Chronic primary low back pain (CPLBP) is a prevalent condition in primary care and a leading cause of disability and absenteeism worldwide. Multidimensional approaches may be necessary to achieve physical and mental health benefits in individuals with CPLBP. **Objective:** The BACKFIT randomized controlled trial aims to evaluate the effectiveness of a multidimensional intervention—combining supervised exercise and mindfulness—on pain, physical fitness, mental health, and functional outcomes in individuals with CPLBP. **Hypothesis:** Both the supervised exercise program focused on motor control and trunk muscle strength (IG1) and the multidimensional intervention combining supervised exercise with mindfulness training (IG2) are expected to produce significant health improvements in individuals with CPLBP. It is further hypothesized that IG2 will yield greater improvements compared to IG1, both immediately post-intervention and at the two-month follow-up. **Design:** Randomized controlled trial. **Setting:** Virgen de las Nieves University Hospital, Granada (Spain). **Participants:** 105 individuals. Inclusion criteria: Previously diagnosed with CPLBP, aged ≥18 and ≤65 years, able to read and understand the informed consent, and able to walk, move, and communicate without external assistance. Exclusion criteria: serious lumbar structural disorders, acute or terminal illness, physical injury, mental illness, and medical prescriptions that prevent participation in the study. **Intervention:** Individuals will be randomly assigned to a supervised physical exercise group (2 days per week, 45 min per session), a multidimensional intervention group (same as supervised physical exercise group, and mindfulness 1 day per week, 2.5 h per session) or an active control group (usual care, 2 days per week, 45 min per session). The intervention will last 8 weeks. **Main Outcome Measures:** Primary outcome: pain threshold, perceived acute pain, and disability due to pain. Secondary measures: body composition, muscular fitness, gait parameters, device-measured physical activity and sedentary behavior, self-reported sedentary behavior, quality of life, pain catastrophizing, mental health, sleep duration and quality, and central sensitization. The groups will undergo pre-intervention, post-intervention, and a 2-month follow-up after a detraining period. **Statistical Analysis:** Both per-protocol and intention-to-treat approaches (≥70% attendance) will be used. Program effects will be assessed via one-way ANCOVA for between-group changes in primary and secondary outcomes. **Conclusions:** Given the complex nature of CPLBP, multidimensional approaches are recommended. If effective, this intervention may provide low-cost alternatives for health professionals.

## 1. Introduction

Low back pain (LBP) is one of the most prevalent chronic pain conditions and the leading cause of years lived with disability worldwide [1]. Its high and growing prevalence across diverse populations poses a major global health challenge, particularly in terms of effective prevention and long-term management [2]. Despite its substantial burden, chronic and non-specific forms of LBP remain insufficiently understood and often suboptimally managed, highlighting the need for evidence-based and individualized therapeutic strategies [3]. Chronic low back pain (CLBP) is defined as pain located between the lower margin of the ribs and the sacral region, lasting more than 12 weeks [4]. It is typically classified as either specific, when a clearly identifiable pathology is present, or non-specific, when no underlying structural cause can be reliably determined. Recently, the World Health Organization (WHO) (2023) [5] introduced the term chronic primary low back pain (CPLBP) to describe persistent or recurrent low back pain lasting more than three months, not attributable to a specific disease (e.g., cancer, infection) or structural abnormality (e.g., fracture, deformity). CPLBP is considered a clinical subset of non-specific chronic low back pain and is often associated with emotional distress and functional impairment. In Spain, the National Health Survey (2023) reported a prevalence of 19.8% for CLBP among individuals aged 15 years and older. This underscores the considerable public health burden of the condition at the national level and reinforces the need for accessible, effective, and evidence-based interventions to mitigate its clinical and societal impact [6].

In the adult population, longer sedentary time has been associated with greater low back pain [7], possibly due to increased stiffness in lower body musculature, impaired blood flow, or poor postural habits derived from prolonged sitting [8,9]. Moreover, individuals with CPLBP often fail to meet the World Health Organization’s physical activity (PA) recommendations (<150 min/week of moderate intensity or <75 min/week of vigorous intensity) and typically engage in lower levels of PA than age-matched healthy peers [10,11,12]. Given that PA contributes to delaying functional decline and improving quality of life, and is closely linked to health parameters in both general and clinical populations [10], it could be particularly relevant to determine, through objective measures such as triaxial accelerometry, the levels of PA and sedentary behavior in individuals with CPLBP. A recent scoping review [13] highlighted the need for greater standardization and methodological rigor in the use of accelerometry in this population, supporting its inclusion in clinical trials focused on PA monitoring.

Evidence-based clinical guidelines for the management of CPLBP support the use of exercise training as a first-line therapy [14,15]. Supervised exercise is considered key for addressing pain and disability. Individuals with CLBP who engage in supervised programs have demonstrated improvements in short- and long-term outcomes such as muscle endurance, pain intensity, functional mobility, flexibility, and quality of life [16]. Although most exercise interventions yield benefits in managing pain and disability in CLBP, effect sizes remain small to moderate, similar to other standard treatments [17,18].

A recent network meta-analysis [19] found that active interventions such as tai chi, yoga, Pilates, sling exercises, and core stabilization were more effective than conventional rehabilitation or no treatment in reducing pain and improving physical function. The authors emphasized the importance of therapies that target core strength and postural control as effective strategies for managing CLBP. Consistently, another network meta-analysis concluded that the most beneficial programs included: (1) at least 1 to 2 sessions per week of Pilates or strength training; (2) sessions lasting less than 60 min focusing on core, strength, or mind-body components; and (3) training durations of 3 to 9 weeks using Pilates or core-based exercises [20].

Additionally, trunk-focused exercise programs have shown positive effects on pain, disability, quality of life, and trunk performance compared to control groups, and superior results in pain and disability when compared to general exercise in individuals with CPLBP [21]. Trunk muscle strength and endurance may also serve as objective indicators in differentiating treatment responses and evaluating the effectiveness of exercise interventions [22]. Furthermore, evidence from young athletic populations supports the clinical relevance of trunk muscle characteristics in LBP. In adolescent gymnasts, an imbalanced flexor-to-extensor strength ratio and reduced lumbar muscle thickness have been associated with CPLBP, suggesting that deficits in trunk muscle function and morphology may represent key targets for rehabilitation [23].

Although recent network meta-analyses have contributed valuable insights into the comparative effectiveness of exercise-based treatments for CLBP, important methodological limitations persist. As highlighted in a previous study [19], considerable heterogeneity exists in terms of intervention type, frequency, intensity, and duration, with many trials implementing very short programs (≤3 weeks) and lacking follow-up measures. The present study aims to address these gaps by combining an 8-week structured exercise intervention focused on trunk muscle strengthening with a 2-month follow-up. This design is expected to provide evidence on the short-term effectiveness and clinical applicability of multidimensional, non-pharmacological interventions in individuals with CPLBP.

Recently, mindfulness has gained recognition within the research and medical communities [24]. Mindfulness meditation might reduce pain and/or the emotional experience associated with it [25,26]. Neuroimaging studies suggest that mindfulness meditation modulates pain by enhancing activity in brain regions involved in cognitive and emotional appraisal (e.g., anterior cingulate cortex, orbitofrontal cortex, right anterior insula), and reducing activation in sensory regions like the thalamus, thus dampening nociceptive signaling to areas such as the somatosensory cortex [26,27]. These effects support mindfulness as a tool for re-evaluating pain experiences. The Mindfulness-Based Stress Reduction (MBSR) program, a structured 8-week intervention, integrates meditation, awareness, and movement practices to improve coping with discomfort and emotional distress. Studies report MBSR benefits for chronic pain, including reduced pain severity, improved mental health, and enhanced quality of life and physical functioning [28,29]. Telehealth-delivered mindfulness has shown promise, yet the impact of in-person programs remains understudied. This study aims to evaluate a supervised, face-to-face mindfulness intervention, hypothesizing enhanced outcomes through therapist support, group interaction, and greater engagement.

Multidisciplinary rehabilitation has been shown to be effective for short- and intermediate-term improvements in pain and function in individuals with chronic musculoskeletal pain [30]. Previous research combining therapeutic exercise and mindfulness reported large effect sizes for functional impairment, pain, kinesiophobia, and physical function, as well as moderate effects for fatigue, anxiety, and depressive symptoms in individuals with fibromyalgia [31]. Compared to usual care, multicomponent treatments demonstrated short-term (up to 3 months) positive effects in these individuals. However, multidimensional approaches have been scarcely studied in individuals with CPLBP. A recent study involving an exercise program and patient education (self-management) highlighted the great potential of these approaches in individuals with CPLBP [32]. Furthermore, an intervention combining exercise and meditation was effective at decreasing self-reported perceptions of LBP from baseline in this population [33]. Similarly, a previous study evaluated an 8-week online program combining MBSR and exercise in adults with chronic pain, reporting high adherence and participant satisfaction [34]. Although no significant differences were found between groups, both groups showed improvements in pain, disability, and pain catastrophizing, supporting the feasibility of integrating mindfulness and exercise in this context. However, few studies have explored multidimensional interventions that combine supervised exercise and mindfulness, particularly in a face-to-face format. The present clinical trial aims to contribute to this emerging field by evaluating the effects of a structured, in-person intervention on a range of physical and psychological outcomes in individuals with CPLBP.

With the aim of understanding the effects and magnitude of these multidimensional programs on health outcomes in individuals with CPLBP, the BACKFIT randomized controlled trial was initiated. The main objective is to determine the effectiveness of a multidimensional program (combining supervised physical exercise and mindfulness), compared to supervised physical exercise alone and an active control group (usual care), on pain and disability (primary outcomes), body composition, muscular fitness, gait parameters, device-measured PA and sedentary behavior, self-reported sedentary behavior, quality of life, pain catastrophizing, mental health, sleep duration and quality, and central sensitization (secondary outcomes) in individuals with CPLBP.

## 2. Methods

### 2.1. Study Design

This study will be a randomized controlled trial (RCT), registered on ClinicalTrials.gov (NCT05443880) with three arms: intervention group 1 (supervised physical exercise), intervention group 2 (supervised physical exercise and mindfulness), and an active control group (usual care). The study will compare the outcomes between these groups in individuals with CPLBP. The study design aligns with the Consolidated Standards of Reporting Trials (CONSORT) guidelines [32]. The Standard Protocol Items: Recommendations for Interventional Trials (SPIRIT) guidelines [35,36] are followed to present this protocol, as detailed in Supplementary Material File S1. The interventions adhere to the Template for Intervention Description and Replication (TIDieR) guidelines [37] for clinical trials, as outlined in the Supplementary Material File S2. A study flowchart is provided in Table 1 and Figure 1.

### 2.2. Participants

This RCT, based on a supervised exercise program and mindfulness intervention, was prescribed and planned by physical therapists and sports science professionals, and it will be conducted in Granada (southeastern Spain). Based on previous literature [22], with a statistical power of 0.80, an alpha error of 0.05, and an effect size of 0.70, a sample size of 26 participants per group is sufficient to find differences in pain after the intervention. Considering a dropout rate of approximately 20–30%, as reported in similar studies involving pain populations [39], the total sample size will be set at 105 participants, randomly assigned to intervention group 1 (IG1, *n* = 35), intervention group 2 (IG2, *n* = 35) and control group (CG, *n* = 35). The inclusion and exclusion criteria are described in Table 2.

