## 4. Statistical Analysis

Since this study aims to determine the potential efficacy and effectiveness of supervised exercise programs and mindfulness, statistical analysis will be performed using both per-protocol and intention-to-treat approaches (with ≥70% attendance required for inclusion). The effects of the intervention will be assessed as between-groups differences in changes from baseline to post-intervention in primary and secondary outcomes using one-way analysis of covariance (ANCOVA). The mean change (post-intervention minus baseline values) will be used as the dependent variable, the group as the fixed factor, and the baseline value of the outcome as a covariate. The same approach will be applied to evaluate the persistence of changes at follow-up. Given the repeated-measures design, linear mixed models will also be used to examine group-by-time interactions across all time points. This approach accommodates missing data under the missing-at-random assumption and accounts for within-subject correlation, providing a more robust framework than ANCOVA for longitudinal analyses. All analyses will be adjusted for potential confounding variables that are not well balanced at baseline. Sex will be used as a potential covariate in all analyses to explore whether the intervention effects differ between men and women, and whenever possible, the sample will be stratified by sex. Cohen’s d will be calculated to determine standardized effect sizes. To control for type I error due to multiple comparisons, the Bonferroni correction will be applied when conducting post hoc analyses or when evaluating multiple outcome variables. Statistical significance will be set at α = 0.05. All analyses will be performed using the Statistical Package for the Social Sciences (SPSS) for Windows, Version 27.0. (IBM Corp., Armonk, NY, USA).

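### The 26 per group in section 2.2 reproduces as a one-sided, uncorrected two-group test; no one-sided test is declared, and the Bonferroni correction in section 4 is not in the sample size

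*Protocol article*

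**What the plan says.** Protocol article, section 2.2 (Participants), sets the power at 0.80 and continues: "an alpha error of 0.05, and an effect size of 0.70, a sample size of 26 participants per group is sufficient" to show a post-intervention difference in pain. It does not name the test, the number of sides, the pair of arms or the scale of the effect size. It then allows for loss: "Considering a dropout rate of approximately 20–30" per cent, and on that basis "the total sample size will be set at 105 participants", 35 in each of three arms.

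Section 4 (Statistical Analysis) plans a one-way ANCOVA of change, with group as the factor and the baseline value as covariate. Linear mixed models are also planned. On multiplicity it says that "the Bonferroni correction will be applied when conducting post hoc analyses or when evaluating multiple outcome variables", and on the threshold that "Statistical significance will be set at α = 0.05". Sidedness is not stated there either. The Abstract names three primary outcomes: pain threshold, perceived acute pain and disability.

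**The concern.** A reader who puts an effect size of 0.70, alpha 0.05 and power 0.80 into a standard two-sample calculation gets 33 or 34 per group, not 26. The calculation also spends the whole 0.05 on one comparison, although three arms give three pairwise contrasts and section 4 promises to correct for them.

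What is at stake is how the result is read. The most demanding hypothesis is that the combined programme (IG2) beats exercise alone (IG1), where both arms receive the same exercise. If that contrast is not significant, the result may be weighed as coming from a trial with 80% power for it. The stated inputs do not establish that power for the planned analysis.

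**Working it through.** **Inputs.** From section 2.2: effect size 0.70 (read as Cohen's d between two groups), alpha 0.05, power 0.80, 26 per group, 35 per arm, dropout about 20–30%. From section 4: baseline covariate, Bonferroni. From section 2.1: three arms, so three pairwise contrasts. Assumed because not stated: two-sided testing, and the size of the Bonferroni family.

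**Step 1: reproduce 26.** The normal approximation is n per group = 2(z_α + z_β)²/d².
- One-sided: 2(1.645 + 0.842)²/0.49 = 25.2, so 26.
- Two-sided: 2(1.960 + 0.842)²/0.49 = 32.0, so 33.

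The exact noncentral t calculation gives 25.94 one-sided (26; power at 26 is 80.1%) and 33.02 two-sided (34). Three-group ANOVA readings do not give 26. Cohen's f of 0.35, 0.33 and 0.286 need totals of about 82, 92 and 122 against 3 × 26 = 78, and f = 0.70 needs only 23 in total.

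**Step 2: power under two-sided testing.** The noncentrality is d√(n/2), which at 26 per group is 0.70 × √13 = 2.52. There is no baseline adjustment in this table.

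| Analysed per arm | alpha 0.05 | 0.05/3 (three contrasts) | 0.05/9 (assumed family) |
|---|---|---|---|
| 24.5 (30% dropout) | 67.0% | 49.3% | 33.6% |
| 26 (stated target) | 69.7% | 52.3% | 36.5% |
| 28 (20% dropout) | 73.0% | 56.2% | 40.3% |
| 35 (no dropout) | 82.3% | 68.2% | 52.9% |

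The effect detectable with 80% power at 26 per group is d = 0.79, 0.92 and 1.04 for the three columns. Keeping d = 0.70 and 80% power would need 34, 45 and 56 analysed per group.

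**Step 3: what the baseline covariate could recover.** If 0.70 is an unadjusted effect and r is the baseline–outcome correlation, ANCOVA works with 0.70/√(1 − r²). The r that restores 80% at 26 per group is √(1 − (0.70/d_detectable)²):
- alpha 0.05: √(1 − (0.70/0.792)²) = 0.47.
- alpha 0.05/3: √(1 − (0.70/0.924)²) = 0.65.

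At r = 0.5 the powers are 81.5% (0.05) and 66.9% (0.05/3). At r = 0.7 they are 93.4% and 85.0%.

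**Step 4: dropout.**
- 26/0.80 = 32.5, so 33 per arm.
- 26/0.75 = 34.7, so 35 per arm.
- 26/0.70 = 37.1, so 38 per arm (114 in total).

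The 35 per arm keeps 26 up to 1 − 26/35 = 25.7% loss. At 30%, 35 × 0.70 = 24.5 remain, and even the one-sided power falls to 77.9%.

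**The case against.** Four points on the other side have weight.

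- **Sidedness.** The article never says two-sided, and its hypotheses are directional. A reader might infer that section 2.2 contradicts a declared two-sided plan. It does not, because none is declared. What stands is that 26 fits a one-sided test, no one-sided test is announced, and the planned three-group F test has no direction.
- **Baseline adjustment.** The powers in the table are those of an unadjusted t-test, and the plan is ANCOVA. A moderate correlation would bring the single two-sided comparison back to 80%. This stands, so it cannot be said that 80% is unattainable. But section 2.2 claims no such gain, states no correlation, and does not say whether 0.70 is a raw or an adjusted effect.
- **Size of the family.** Section 4 does not fix the number of tests. Nine tests (three outcomes by three contrasts) is one reading, and the exact family may lie in an analysis plan that is not shown. The 37% is therefore illustrative. The three-contrast figure needs only the three arms and the stated correction of post hoc comparisons.
- **Dropout.** The range is approximate, and 35 per arm covers its midpoint. A reader might infer that the allowance is simply wrong. The shortfall appears only above 25.7%, and at 30% it is 1.5 participants per arm.

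**Conclusion.** The point holds in a limited form. The stated 80% power at 26 per group matches a one-sided, uncorrected two-group comparison, and it is not supported for the analysis in section 4 as the article describes it. Under the conventional two-sided assumption, and before any covariate gain, power at d = 0.70 is about 70% for one uncorrected contrast and about 52% with Bonferroni over three. If the family is taken as nine tests, an assumption, it is about 37%. Across the stated dropout range the first two figures run from 73% and 56% (20% loss) to 67% and 49% (30% loss). The 70% is the uncorrected figure and should not be read as already including Bonferroni.

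The documents do not support the stronger conclusion that the trial certainly lacks 80% power, or that it must recruit more. That depends on the baseline correlation, the scale of the 0.70 and the family of tests, none of which is given.

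**What to change.** Keep 105 participants and rewrite the sample-size paragraph in section 2.2 so that it states:

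1. the test, the number of sides, the contrast and the alpha actually used, consistent with the Bonferroni rule in section 4;
2. the power or detectable effect these deliver at 26 analysed per group. For a two-sided unadjusted test this is about 70% (d = 0.79) for one contrast, or about 52% (d = 0.92) with correction over three;
3. the assumed baseline–outcome correlation and its source, if 80% is meant to rest on ANCOVA;
4. that 35 per arm allows for up to about 25% dropout, with the power remaining at 30%.

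The cost is one paragraph and a less favourable stated power. Recruitment, conduct and outcomes do not change.

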The CG will receive the usual care provided by the Physical Medicine and Rehabilitation Service. Participants will follow the same session structure described above twice per week (45 min per session) for 8 weeks. All participants will perform 1 set of 10 repetitions or 60 s per exercise, followed by 60 s of rest. Execution speed will be individualized. Intensity will be assessed with an RPE scale (≥5 RPE). Sessions will include: warm-up (5 min: postural awareness, diaphragmatic breathing, costal breathing, transversus abdominis contraction, pelvic swing); main activity (35 min: lower/upper abdominis exercise, hip abduction with knee extension, cat-camel exercise, alternate arm/leg elevation in quadruped, bird-dog); and cool-down (5 min: lumbosacral, psoas, hamstring, and pyramidal muscle stretching, bird-dog, and lumbosacral stretching on the floor). All of them will be performed in supine or quadrupedal position. Although active, this protocol reflects hospital standard rehabilitation care. Including it in the control group meets ethical and organizational requirements, ensuring participants are not deprived of care, allowing a more rigorous comparison with the multidimensional intervention.

This program allows adaptations for practical evidence-based aspects, such as performing an alternative exercise targeting the same muscle group without causing pain or changing the plane of movement. Adverse events, effects, or health issues attributable to the testing or intervention sessions, along with their severity and resolution, will be recorded by a researcher responsible for auditing the assessment team. If an adverse event prevents participation, temporary or permanent exclusion will be discussed and documented. Temporary exclusions require medical clearance for return.

This study was approved by the Clinical Research Ethics Committee of Granada, Government of Andalusia, Spain (code: 2255-N-21). It will be conducted following the ethical principles of the Declaration of Helsinki (1964 and later amendments). No formal audit is scheduled for this clinical trial.

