## 5. Discussion

This paper outlines the protocol developed by a multidisciplinary team of experts in Physical Therapy and Sports Sciences, aimed at determining the effects of a supervised exercise intervention and mindfulness (i.e., a multidimensional approach) on health outcomes in individuals with CPLBP, an area that remains relatively underexplored. In line with the latest WHO guidelines, which highlight the complexity and heterogeneity of mechanisms involved in CPLBP, multimodal and multidisciplinary interventions are recommended over isolated treatments for individuals who do not respond adequately to single modalities. These approaches not only aim to enhance therapeutic effectiveness but may also contribute to reducing future clinical costs and long-term healthcare needs [32]. Previous studies support the use of integrative, non-pharmacological strategies to address both the physical and psychological dimensions of chronic pain [19,24,83]. Based on this rationale, the present protocol combines supervised physical exercise and mindfulness to simultaneously address multiple health-related outcomes. It is expected that both intervention groups will show improvements in pain, disability, trunk muscle function, physical fitness, gait, PA levels, sedentary behavior, sleep duration and quality, mental health, and quality of life compared to the standard exercise care group. Furthermore, greater improvements are anticipated in the group receiving the combined intervention (IG2), particularly in outcomes related to pain, psychological well-being (e.g., pain catastrophizing, mental health), sleep quality, and central sensitization.

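### The 80% power claim rests on one effect size of 0.70 tied to no pair of arms, and 0.70 cannot describe all three ordered contrasts

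*Protocol article*

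**What the plan says.** The sample size paragraph (section 2.2) takes a power of 0.80 and an alpha of 0.05 and, citing an earlier study, states that with "an effect size of 0.70, a sample size of 26 participants per group is sufficient to find differences in pain after the intervention". It then allows for 20–30% dropout and sets 35 per arm, 105 in total. No pair of arms is named, and no particular pain measure. Section 4 adds only "Statistical significance will be set at α = 0.05", with a Bonferroni correction for post hoc comparisons or multiple outcomes. Sidedness is not stated.

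The trial asks more than one question. The main objective (end of section 1) sets IG2 against both IG1 and CG. The abstract hypothesises that IG2 will do better than IG1. The Discussion (section 5) expects both intervention arms to improve more than standard exercise care, and IG2 to improve most.

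CG is active. Section 2.4 says of it: "Participants will follow the same session structure described above twice per week (45 min per session) for 8 weeks". Its intensity floor is RPE 5, and Table 3 lists motor control exercises for it as well as for IG1.

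On the size of exercise effects in chronic low back pain, the Introduction says that "effect sizes remain small to moderate, similar to other standard treatments". Of an online programme combining MBSR and exercise it reports: "Although no significant differences were found between groups, both groups showed improvements in pain, disability, and pain catastrophizing".

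**The concern.** A power statement belongs to a contrast. Here one number serves a three-arm design in which the protocol predicts an order. Differences between ordered means on a common SD add up, so a single 0.70 cannot be the effect for IG1 vs CG, IG2 vs IG1 and IG2 vs CG at once. Whichever contrast it belongs to, at least one other has a different effect and a different power, and the protocol says nothing about those.

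The active control sharpens the point. A comparator with the same frequency, session length and duration as IG1, and partly shared content, gives some reason to expect a modest IG1 vs CG difference, and the Introduction's own summary points the same way.

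What is at stake is interpretation. A reader of section 2.2 would take every pairwise comparison of pain to have 80% power and would weigh a non-significant result accordingly. For at least one contrast that weight may be undeserved.

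**Working it through.** **Inputs.** From section 2.2: effect 0.70, power 0.80, alpha 0.05, 26 evaluable per arm, 35 randomised per arm. From the abstract and section 5: order IG2 > IG1 > CG. From section 4: ANCOVA with baseline as covariate, and Bonferroni. The baseline–outcome correlation is not given; r = 0.5 is used below as an assumption where stated.

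**Step 1: reproduce the 26.** Normal approximation, n per group = 2(z₁₋α + z₁₋β)²/d².
- One-sided: 2(1.645 + 0.842)²/0.49 = 25.2, so 26. The t-test gives 25.9, so 26.
- Two-sided: 2(1.960 + 0.842)²/0.49 = 32.0, rounded up to 33. The t-test gives 33.02, so 34.
- Two-sided with ANCOVA, effect d/√(1 − r²): at r = 0.5, 0.70/0.866 = 0.808, giving 26.

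The stated figure therefore fits one pair of arms tested one-sided, or two-sided with an unstated correlation of about 0.5. At 26 per arm and d = 0.70, unadjusted power is 80.1% one-sided and 69.7% two-sided.

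**Step 2: additivity.** With a common SD, d(IG2 vs CG) = d(IG2 vs IG1) + d(IG1 vs CG).
- Reading A, 0.70 is IG2 vs CG: the adjacent effects sum to 0.70, so at least one is ≤ 0.35.
- Reading B, 0.70 is each adjacent contrast: IG2 vs CG = 0.70 + 0.70 = 1.40.

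**Step 3: power for one uncorrected pair (t-test).**

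| d | 26 per arm, one-sided | 26 per arm, two-sided | 26 per arm, two-sided at 0.0167 | 35 per arm, two-sided |
|---|---|---|---|---|
| 0.20 | 17.5% | 10.9% | 4.6% | 13.1% |
| 0.35 | 34.5% | 23.6% | 12.2% | 30.3% |
| 0.50 | 55.3% | 42.4% | 26.0% | 54.1% |
| 0.60 | 68.8% | 56.4% | 38.5% | 69.7% |
| 0.70 | 80.1% | 69.7% | 52.3% | 82.3% |

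At d = 0.35 and 26 per arm, ANCOVA with r = 0.5 raises two-sided power to 29.8%. Combining all the favourable choices (35 per arm retained, one-sided, ANCOVA with r = 0.5) gives 51%. The shortfall at 0.35 therefore does not come from sidedness, dropout or lack of adjustment.

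**Step 4: the split under reading A.** The order fixes the sum, not the shares. With 0.35 and 0.35, both adjacent contrasts have 34.5% one-sided power at 26 per arm. With IG1 vs CG = 0.10 and IG2 vs IG1 = 0.60, IG2 vs IG1 has 68.8% one-sided power. With IG1 vs CG = 0.50 and IG2 vs IG1 = 0.20, it has 17.5%.

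**Step 5: detectable d at 80% power, two-sided, unadjusted.**

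| | 26 per arm | 35 per arm |
|---|---|---|
| alpha 0.05 | 0.79 | 0.68 |
| alpha 0.05/3 = 0.0167 | 0.92 | 0.79 |

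**The case against.** A reader might infer that 80% power cannot hold for IG2 vs IG1 or for IG1 vs CG. The documents do not go that far. Section 2.2 names no contrast. Under reading B, one-sided power is at least 80% for every pair. The source of the 0.70 is a cited study whose contrast is not described. What stands against reading B is only that an effect of 1.40 over an active exercise control fits poorly with effects the protocol calls small to moderate.

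A reader might also infer that IG2 vs IG1 is one of the small contrasts, so that a null result there is likely even if mindfulness helps. That does not follow either: only one adjacent contrast has to be 0.35 or less, and it may be IG1 vs CG.

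Nor is CG a same-dose copy of IG1. Frequency, session length and duration match, but in phases 3 and 4 (4 + 5 = 9 of 16 sessions) IG1 moves to RPE 6 or more with load or unstable surfaces, while CG stays at a floor of 5 in supine or quadruped positions.

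The protocol's evidence is also mixed. It cites large effects of combined exercise and mindfulness in fibromyalgia and better results for trunk-focused than general exercise. The null study it describes was delivered online.

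Finally, a journal article may leave contrast-by-contrast power to a fuller document. That would excuse silence, but section 2.2 makes a positive claim of sufficiency, and that claim is what is at issue. No passage plans to read non-significance as equivalence, so the risk of misreading is a reasonable worry and not something the protocol commits to.

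**Conclusion.** The point holds in limited form and should be corrected. The 80% claim is attached to no contrast, and one effect of 0.70 cannot serve all three under the protocol's own ordering.

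If 0.70 is IG2 vs CG, at least one adjacent contrast has power of at most 34.5% one-sided or 23.6% two-sided at 26 per arm. If it is each adjacent contrast, the protocol implies 1.40 for IG2 vs CG and does not support it. Separately, even a true 0.70 yields 69.7% two-sided at 26 per arm without adjustment.

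These figures assume a common SD, the stated ordering, and one uncorrected, unadjusted test. Power for IG2 vs IG1 specifically cannot be fixed from the documents; it depends on a split they do not give.

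**What to change.** Keep 35 per arm. In section 2.2:
- Name the pair of arms, the pain measure and the sidedness to which 0.70 applies. The sponsor must supply these; they cannot be read off the article.
- Replace the general 80% statement with the detectable d at 80% power for every pairwise contrast, using the step 5 values: two-sided 0.79 (26 per arm) and 0.68 (35 per arm), or 0.92 and 0.79 at the Bonferroni level for three pairs.
- State that 80% at d = 0.70 with 26 per arm holds only one-sided, or two-sided with an assumed baseline correlation of about 0.5.

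In section 4, add that all pairwise contrasts will be reported with 95% confidence intervals and that a non-significant contrast will not be read as no effect.

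The cost is a few sentences and no extra participants. The downside is that the stated power becomes less favourable.
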